### Intervention

*Group A* (ISI score under 8) will be observed longitudinally through standard of care above-described procedure, without an active intervention. *Group B* (ISI score above 7) will be randomly assigned to 2 active interventions both conducted through digital therapy: (1) psychoeducation based on CBT-I adapted for pregnancy (experimental intervention; subgroup B2); (2) information on sleep disorders and on peripartum-related issues (placebo intervention; subgroup B1).

Each intervention will share the following characteristics:

fully digitalized on the study website;composed of 6 weekly 20-minutes online sessions;each session will include a before and after brief survey to monitor satisfaction;each participant will start the intervention upon completion of the baseline assessment;participants will be asked to fill out directly on the website a reduced version of the sleep and emotion diaries each day during the intervention (6 weeks).

For Group B1 (placebo), each session will include: educational videos (ca. 20 min) on aspects related to pregnancy and sleep; brief feedback questions. Participants in the placebo intervention will not be given specific indications on skills or techniques for sleep difficulties and will not have access to the weekly chat with the clinician.

Sessions will cover the following contents:

Session 1: phases of pregnancy;Session 2: sleep disorders;Session 3: nutrition and physical activity during pregnancy;Session 4: childbirth;Session 5: psychophysical development of the child in the first year of life;Session 6: synthesis of previous sessions.

For Group B2 (intervention), each session includes: brief videos delivering the intervention content (ca. 20–30 min); short questions aimed at raising awareness of how the content of the videos related to participants’ experience (e.g., one own dysfunctional beliefs and attitudes about sleep); short feedback questions; downloadable information (pdf) on sleep education and CBT-I derived techniques adapted to pregnancy. The downloadable information associated with each session are chapter of a psychoeducational book (the table of contents, which follows the video contents, are available in Supplementary file S2). Each session would require around 30 min a week. Participants will be given opportunity to raise concern or difficulties with the content of the intervention and with the filling of sleep diaries, both as feedback before and after each session and with weekly opportunity to directly chat with a clinician through the web site.

Session 1: Presenting the aims of the intervention and introducing psychoeducation on physiological regulation of sleep, on sleep health and on how sleep changes during pregnancy;Session 2: Psychoeducation on psychological regulation of sleep; impact of behaviours on sleep regulation; introduction on sleep compression and stimulus control;Session 3: Psychoeducation on cognitive factors maintaining sleep difficulties; introduction on cognitive restructuring;Session 4: Psychoeducation on emotional factors maintaining sleep difficulties and on the bidirectional association between sleep and emotions; introduction “into” or “on” emotion regulation techniques;Session 5: Psychoeducation on sleep in the postpartum and on the development of sleep regulation in children;Session 6: Relapse prevention and focus on acquired skills and on how to prioritize sleep.

Adherence will be monitored through weekly chat with a licensed psychotherapist expert in CBT-I ([name]) and through diary completion during the six weeks of the intervention. Strategies to improve adherence will be implemented during the weekly chat and include: reviewing week sleep diaries, identifying barriers and resistance, rediscussing any technical difficulties with the online sessions. The availability of direct contact will also serve to assess any difficulty with specific psychoeducational content and to modulate the intervention accordingly.

#### Follow-up-1

After 6 weeks from baseline (post-treatment for *Group B*), participants will be assessed trough the sleep and emotions diaries and the actigraphic monitoring. Participants who consented to the treatment of salivary samples will be asked to collect their sample through salivary swabs the first day of EMA in the 2 time-points of morning and evening. Participants will also be asked to fulfil a set of questionnaires (described in “Assessments”). The EMA week will thus follow the same procedure of the baseline assessment.

#### Follow-up-2

After 12 weeks from baseline, participants will be asked to log-in to their personal area on the website and complete a set of questionnaires.

#### Follow-up-3

Between 1 and 2-week after birth, participants will be asked to log-in to their personal area on the website and complete a set of questionnaires, including information on birth (type of birth, length of labour, self-perception of stress and fatigue during birth) and on the newborn (weight, Apgar Index, specific problems after birth). Information on feeding modality and mothers’ related feeling will be collected.

#### Follow-up-4

Three months post-partum, participants will be asked to log-in to their personal area on the website and complete a set of questionnaires. Specific information on the experience of motherhood will be asked, including: mother-infant attachment, maternal perceived stress, feeding modality and maternal related feeling. Paternal perceived stress will also be part of the assessment.

#### Follow-up-5

Six months post-partum, participants will be again observed trough the EMA week, following the procedure of the Baseline and Follow-up 1 phases, with also a sleep diary for their children. Participants will also be asked to fill a set of questionnaires, including information on the child’s temperament and on maternal and paternal experiences.

### Outcomes

#### Primary outcomes

Stress reactivity: salivary cortisol level assessed by saliva sample provided by participants through swabs twice a day once at baseline, follow-up 1 and 5.Sleep efficiency: Total Sleep Time (min)/Time In Bed (min) expressed in percentage and assessed trough actigraphy monitoring. Assessed one week at baseline, follow-up 1, follow-up 5.Depressive symptoms: Edinburgh Postnatal Depression Scale (EPDS) [43] total score. EDPS scores > 10 will be considered as indicative of PND. Assessed at baseline, follow-up 1 and 5.Mothers’ Insomnia symptoms: Insomnia Severity Index (ISI) [39] total score. Assessed at baseline, follow-up 1–5.Anxiety symptoms: Generalized Anxiety Disorder questionnaire (GAD-7) [44] total score. Assessed at baseline, follow-up 1–5.Valence of affective states at morning and evening: visual scale in sleep and emotional diaries. Assessed one week at baseline, follow-up 1, follow-up 5.Arousal of affective states at morning and evening: visual scale in sleep and emotional diaries. Assessed one week at baseline, follow-up 1, follow-up 5.Emotion regulation strategies: Cognitive Emotion Regulation Questionnaire – Italian Short-Version (CERQ-IS) [45] subscales scores. Assessed one week at baseline, follow-up 1, follow-up 5.

#### Secondary outcomes

Maternal post-partum stress: Parenting Stress Index (PSI) [42] total score. Assessed at follow-up 3–4.Fathers’ Insomnia symptoms: ISI total score. Assessed at baseline, follow-up 1–5.Children sleep difficulties: Brief Infant Sleep Questionnaire (BISQ) [46] total score. assessed at follow-up 3–5.

#### Additional outcomes

Biomarkers of prenatal sleep alteration: DNA methylation of the genes FKBP5, BDNF and NR3C1 (see “Salivary samples”). Assessed at baseline.

### Assessments

#### Self-report questionnaire

Self-report questionnaire will be filled by participants directly on the website and their responses associate with their unique ID-code. Instruments used and timeline are reported in Table 1.

**Table 1. Tab1:**
[figure not shown]
Questionnaire and measurement points

*Abbreviations*: *BSL *Baseline, *INT *Intervention, *FU F*ollow-up

*Subgroup B2 will complete the Dysfunctional Beliefs and Attitudes about sleep during session 3 of the intervention

#### EMA week

At Baseline, Follow-up 1 and Follow-up 5 participants will be observed for a 7-day EMA procedure.

The procedure is synthetized in Fig. 3 and include the following assessments:

**Fig. 3 Fig3:**
[figure not shown]
Graphic outline of the procedure for the ecological-momentary-assessment (EMA) week

#### Sleep and emotion diaries

The sleep diary will be filled online through the website and is developed in accordance with the norms for the “consensus sleep diary” [47]. The sleep diary is a calendar-style form in which information about sleep is reported every morning within 30 minutes of the last awakening and every evening at bedtime. The diary will include further assessment of emotional processes associated with sleep. Sleep variables will include: sleep onset latency (SOL), wake after sleep onset (WASO), total sleep time (TST), time in bed (TIB), sleep efficiency index (SEI). Moreover, the level of alertness (low energy-high energy) and the valence (positive-negative) and arousal (calm-agitated) of affective states in the evening and in the morning will be collected through visual scales [48].

#### Wrist actigraphy

Women will be asked to wear an actigraphy in their non-dominant hand for 7 days, during both day- and night-time. The actigraphy is a small, computerized wristwatch-like device used to detect sleep-wake activity. The actigraphy is an ecological and non-invasive device, with different models validated to evaluate sleep (SOL, WASO, TST, TIB, SEI) and wake (mean physical activity) parameters [49]. We will use the Micro Motionlogger actigraph (Ambulatory Monitoring, Ardsley, NY, USA), which has good agreement with polysomnography [50] and is widely used to detect sleep-wake activities in different populations [51, 52]. Data from actigraphic recordings will be scored by two trained investigators ([name], [name]) following decision by consensus.

#### Salivary samples

Salivary samples will be self-collected at home from consenting participants through a salivary swab the first day of each EMA week in 2 time-points (morning and evening). Samples will be used to evaluate salivary cortisol levels by liquid chromatography-tandem mass spectrometry (LC-MS/MS). Cortisol levels will be used as index of stress reactivity. Moreover, a cytobrush will be used to collect exfoliated cells from oral mucosa (1 assessment per person) and used for the analysis of DNA methylation of the genes FKBP5, BDNF (brain derived neurotrophic factor), and NR3C1 (glucocorticoid receptor), by bisulfite next-generation sequencing. These genes have been validated as intergenerational stress-related gene [22–24, 53, 54]. Here we will test the DNA methylation pattern of these genes as a potential biomarker of prenatal poor sleep, which is considered a stressing factor.

Since saliva and blood methylation patters are largely overlapping [55], we will use saliva samples to validate a new and easily applicable biomarker of prenatal stress.

The two biomarkers of parental stress (cortisol levels and methylation of the genes FKBP5, BDNF, and NR3C1) will be evaluated as outcome for the psychological intervention for insomnia.

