### Statistical analysis

Analyses will be performed by a professional biostatistician ([name]). For all outcomes, intent-to-treat analyses (ITT) will be performed including all randomized women in the statistical analyses. Descriptive statics will be reported, including recruitment rate, dropout rate, and data completion rate. A detailed flow chart of study participants will be provided. Only data from those completing the trail will be analysed. Baseline characteristics of non-completers and completers will be compared. Independent t-test and Chi-square test will be conducted to compare randomized groups on baseline characteristics. Significant differences between dropouts and retained participants will be investigated with comparisons on baseline and outcome characteristics. Multivariate linear regressions will be used for testing associations with insomnia during pregnancy and postpartum depression. A multivariate mixed effects model analysis will be performed to test the interventions efficacy over time. Within- and between-groups differences will be measured including as factors the Group (A, B1, B2) and TIME (Pre-; Post-; last weeks of pregnancy; Birth; 3; 6) and as outcome all endpoints which will be collected at all assessments. For all analyses statistical significance is set at p-values < 0.05.

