In conclusions, MOTHERS has several strengths and implications for familiar wellbeing in the peripartum. The intervention is innovative as it focuses not on a restricted series of sleep hygiene rules, which may be not appropriate for some individuals, but on overall promotion of sleep health, delivering knowledge and promoting attitude to self-manage sleep health. It is founded on the concept of sleep health as a positive construct [58] and on the 5 principles of good sleep health, which are universally adoptable and thus suited for different conditions [78]. It also includes basic information derived from models of insomnia disorder about behavioural, emotional, and cognitive processes influencing sleep health, and adapted CBT-I techniques to modify sleep-disrupting processes. The study includes assessments at the biological (salivary sample), physiological (actigraphy), and self-report data to broader the understanding of the multiple complex impact of sleep health and its promotion during pregnancy. We also included a pre- and post-intervention assessment and 4 follow-ups to tackle short- and long-term effects of the MOTHERS programs and the longitudinal psychobiological changes in sleep and wellbeing across pregnancy. The inclusion of assessment of partners’ and children’s sleep and wellbeing aims to further deepen the understating of sleep and psychopathology in the family context. Furthermore, intergenerational effects of maternal sleep and stress on children’s sleep problems and overall health will be assessed though questionnaire and diaries, and a new biomarker of maternal poor sleep as a stressing condition will be tested (the DNA methylation of the FKBP5, BNDF, and NR3C1 genes).

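### One baseline measurement of three genes, each open to testing at p < 0.05 with no family control, is said to validate a biomarker; the design supports only a candidate

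*Protocol article*

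**What the plan says.** Under *Additional outcomes* the protocol article lists "Biomarkers of prenatal sleep alteration: DNA methylation of the genes FKBP5, BDNF and NR3C1 (see “Salivary samples”). Assessed at baseline". That is a third tier, below the primary and secondary outcomes.

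Under *Salivary samples* it says that oral mucosa cells are collected once per person and that methylation is read "by bisulfite next-generation sequencing". The number of CpG sites or regions per gene is not given. The purpose is then stated in two strengths. First: "Here we will test the DNA methylation pattern of these genes as a potential biomarker of prenatal poor sleep". In the next paragraph, after a remark that saliva and blood methylation largely overlap: "we will use saliva samples to validate a new and easily applicable biomarker of prenatal stress".

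*Expected results and discussion* says that "a new biomarker of maternal poor sleep as a stressing condition will be tested". *Statistical analysis* closes with "For all analyses statistical significance is set at p-values < 0.05" and names no family of tests and no adjustment.

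**The concern.** Two things are stated, not merely left out: a per-test threshold that covers every analysis, and validation as the conclusion to be reached. Together they allow three separate chances of a significant gene at the full 0.05 level, and they attach to the result a word that normally implies confirmation in independent data. One cross-sectional measurement in one sample can put forward a candidate marker. It cannot also confirm it.

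The biomarker appears in the abstract and is presented as new in the closing discussion, so a chance finding at one gene could be reported with more weight than the design can give it.

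**Working it through.** **The plan's own figures.** The article states no family-wise error rate and no sample size for methylation. The one related figure that can be recalculated is recruitment: 114 / (1 − 0.24) = 150, which matches. That calculation is for the depression scale (EPDS), so it gives no assurance about the methylation tests.

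**Inputs**
- Tests: 3, one per gene (*Additional outcomes*).
- Level per test: 0.05 (*Statistical analysis*). Sidedness is not stated; two-sided is assumed.
- Group sizes: A = 38, B = 76 (*Screening*). The number with methylation data is not fixed: the planned intake is 150, and use of the samples needs separate consent (*Screening*, *Baseline*).
- Correlation between gene-level tests: not given; a range is shown.

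**Step 1: three gene-level tests, no true association.** If independent, P(at least one p < 0.05) = 1 − 0.95³ = 1 − 0.857 = 14.3%. With equally correlated normal test statistics, by simulation of the chance that the largest |z| exceeds 1.96:

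| Correlation | Chance of at least one false positive |
|---|---|
| 0 | 14.3% |
| 0.3 | 13.6% |
| 0.5 | 12.5% |
| 0.6 | 11.8% |
| 0.8 | 9.8% |

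This is two to three times the nominal 5%, and it needs no assumption about CpG sites.

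**Step 2: more tests (hypothetical counts).**
- Three genes by the three pairwise contrasts of A, B1 and B2 would be 9 tests: 1 − 0.95⁹ = 37.0% if independent, 23.6% at correlation 0.6.
- Five sites per gene (15 tests): 54%, 36% and 20% at correlations 0, 0.5 and 0.8.
- Ten sites per gene (30 tests): 79%, 51% and 26% at the same correlations.
- With independent tests the chance first passes one half at 14 tests: 1 − 0.95¹³ = 48.7%, 1 − 0.95¹⁴ = 51.2%.

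**Step 3: effect of adjustment.** The strictest Holm step over three genes is 0.05 / 3 = 0.0167. When no gene is associated, the family-wise error is 1 − (1 − 0.0167)³ = 4.9% for independent tests.

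**Step 4: cost in power.** For Group A v Group B the standard error of a standardised difference is √(1/38 + 1/76) = 0.199. For an assumed difference of 0.6, 0.6 / 0.199 = 3.02. Power at 0.05 is Φ(3.02 − 1.96) = 85.5%; at 0.0167 it is Φ(3.02 − 2.39) = 73.4%. For assumed differences of 0.5 and 0.7, power falls from 71.1% to 54.9% and from 94.1% to 87.1%.

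**The case against.** The strongest reply is that the article is mostly modest on this point. Methylation is an additional outcome, it is called a potential biomarker just before the strong sentence, and the discussion says only that it will be tested. The three genes were chosen from cited work, so this is not an open-ended screen. The sentence with the strong verb is partly a justification for using saliva. CpG regions, summary measures and adjustment for such an outcome often sit in an analysis plan or laboratory plan that is not shown, and a general 0.05 level does not by itself rule out adjusted p-values.

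Most of this stands, and it limits the point. The absence of site-level detail is not a finding. Three stronger readings are tempting and should not be drawn:
- A reader might infer that a false biomarker claim is likely. For the three named genes the chance is about 10 to 14%; a figure above one half needs test counts that the article never gives.
- A reader might infer that one significant CpG would count as validation. No section sets such a criterion, and the reference to the methylation pattern of the genes does not commit to site-by-site tests.
- A reader might infer that nothing tempers the claim. The outcome rank and the word *potential* do so in part.

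The reply does not remove the conflict between potential and validated within one section, nor the fact that a threshold for all analyses is stated with no family control. An unseen plan could adjust the p-values, but it would not change the published statement of what the analysis will show.

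**Conclusion.** The point holds in a limited form. The article claims validation from a single baseline measurement in one sample with no replication set described, and this conflicts with its own more cautious wording. Under the stated threshold, three gene-level tests carry a family-wise error of 14.3% if independent and about 10 to 12% if correlated at 0.8 to 0.6. These figures assume one test per gene, no true association and unadjusted p-values. Testing sites or contrasts singly would raise the error by an amount that the article does not allow anyone to fix. Because the outcome is third tier, this should be corrected, but it does not threaten the main trial comparison.

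**What to change.** In *Salivary samples*, replace the verb *validate* with wording such as: *explore as a candidate biomarker, to be confirmed in an independent sample*.

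If a significance claim is kept, state in *Statistical analysis* that it rests on one summary methylation value per gene, for one named baseline contrast (for example Group B v Group A, or the association with baseline ISI), with Holm adjustment over the three genes. Label any site-level results exploratory.

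No extra assays or women are needed. The costs are a more modest claim and the loss of power shown above: about 12 percentage points at the strictest Holm step for an assumed difference of 0.6 (85.5% − 73.4% = 12.1).

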### Study aims

The present trial aims to evaluate the long-term effectiveness of digital psychoeducational module based on CBT-I for expectant mothers complaining insomnia symptoms without comorbid somatic or mental disorders on:

physiological, biological, genetical and subjective indices of maternal psychopathology (perinatal depression and anxiety), stress, and emotional processes; these will be assessed through cortisol levels, recording of the sleep-wake activity through actigraphies, sleep diaries, and online questionnaires;father’s and new-born’s sleep and perceived parental stress; these will be assessed through online questionnaires and sleep diaries.

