### Baseline

All participants will be asked to log-in to the study website using their personal credentials and to fill in a set of questionnaires (described in “Instruments”). Participants’ sleep and emotional processes will be monitored for 7-days through an ecological-momentary-assessment (EMA) design, which allows repeated experience sampling [40]. The EMA week will include: sleep and emotions diaries (in the morning and evening) to be completed on the website; an actigraphic (wearable wrist device) monitoring sleep-wake variables for 7 days. Under express and separate consents, on the first day of the EMA week, women will be trained to collect, at their home, saliva sample through the saliva swabs they received in their folder. Collection will be carried on in 2 time-points during the day: immediately after awakening and just before bedtime. The saliva sample will be used for evaluation of cortisol levels and for the analysis of DNA methylation of genes involved in the stress response: the FKBP5, the BDNF, and the NR3C1 [41]. Rationales for these analyses are described in “Outcomes”.

Participants will store their samples at home. At the end of the EMA week, participants will be given appointment with the researchers to bring the actigraphy and the saliva samples, closed in an envelope and already marked with unique ID-code.

Participants will be explained that their partners could also take part to the study under their expressed informed consent. Women will be given an informative form directed to partners. Within 3 days from the screening, participants will be contacted via e-mail to assess if their partners are interested to participate. In case of interest, partners’ contacts will be asked. Interested partners will receive an e-mail with their unique credentials to log-in to the website and express their informed consent. In their personal area of the website they will be asked to complete, at each phase of the study, a set of questionnaires: socio-demographic variables for Baseline; the ISI for Baseline and Follow-ups 1–5, a 7-day sleep diary for Baseline and Follow-ups 1 and 5; the Parenting Stress Index (PSI) [42] at Follow-ups 3–5. Participants and partners will be matched through an ID-code and will access their respective unique personal area on the website.

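### DNA methylation is named an outcome of the intervention but is sampled only at baseline, before the intervention starts, so no treatment effect on it can be shown

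*Protocol article*

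**What the plan says.** The protocol article gives methylation two roles.

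- **Intervention outcome.** The last sentence of Salivary samples takes cortisol and the methylation of the three genes together and says they "will be evaluated as outcome for the psychological intervention for insomnia". Study aims says effectiveness will be evaluated on "physiological, biological, genetical and subjective indices of maternal psychopathology", among other indices.
- **Biomarker of poor sleep.** Additional outcomes heads the measure "Biomarkers of prenatal sleep alteration: DNA methylation of the genes FKBP5, BDNF and NR3C1". The Abstract, an earlier sentence of Salivary samples and the closing discussion describe it in the same way.

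The sampling is stated explicitly.

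- Salivary samples: "a cytobrush will be used to collect exfoliated cells from oral mucosa (1 assessment per person".
- Additional outcomes: "DNA methylation of the genes FKBP5, BDNF and NR3C1 (see “Salivary samples”). Assessed at baseline", with no later visit named.
- Baseline: saliva from the baseline week is used for cortisol and "for the analysis of DNA methylation of genes involved in the stress response: the FKBP5, the BDNF, and the NR3C1".
- Intervention: "each participant will start the intervention upon completion of the baseline assessment". The Procedure section likewise calls baseline pre-treatment and follow-up 1 post-treatment for Group B.

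Cortisol has a different schedule. Primary outcomes lists it at baseline, follow-up 1 and follow-up 5.

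**The concern.** An outcome of an intervention has to be measured after the intervention has had a chance to act. Methylation is measured only before. The sentence that makes it an outcome pairs it with cortisol as though the two were sampled alike, and they are not.

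At stake is what the trial may claim. A reader or analyst who takes the outcome sentence at face value could report a baseline contrast between B2 and B1 as an epigenetic effect of the programme, or a null contrast as evidence that there is none. The data could support neither statement.

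**Working it through.** The plan states no figure for this point, so there is none to reproduce. The check is of the schedule, followed by one short calculation.

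**Step 1. Count the measurements per woman.**

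| Measure | Before treatment | After treatment | Source |
|---|---|---|---|
| Methylation | 1 (baseline) | 0 | Additional outcomes; Salivary samples |
| Cortisol | baseline | follow-up 1, follow-up 5 | Primary outcomes |

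For methylation, one assessment in total minus one at baseline leaves 1 − 1 = 0 after treatment.

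**Step 2. What can be estimated.** A change from baseline needs two measurements, and there is one. A comparison between arms after treatment needs a post-treatment measurement, and there is none. The only available B2–B1 contrast is the baseline one. Because B1 and B2 are formed by randomisation and neither has begun its sessions, the true treatment effect in that contrast is zero.

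**Step 3. What a test of that contrast would do.** Inputs: 38 women per arm (Randomization section); significance level 0.05 (Statistical analysis section), taken as two-sided, which the article does not state; true difference 0.

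- Probability of rejection in each tail: 0.025.
- Both tails: 2 × 0.025 = 0.05.
- With 1,000 per arm instead of 38: again 0.05.

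The rejection rate equals the significance level whatever the sample size. Recruiting more women cannot cure the problem.

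**Step 4. Look for a later methylation sample.** Saliva is collected again at follow-up 1 and follow-up 5, and the Baseline section names saliva as a source for methylation. But Additional outcomes and Salivary samples limit methylation to baseline and to one assessment. No section schedules a methylation assay after treatment.

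**The case against.** Four arguments can be made on the other side.

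1. **Most of the article already treats methylation as a biomarker only.** This is right. The Abstract, Additional outcomes, part of Salivary samples and the closing discussion all do so, and where the discussion sets out the expected effects of treatment, the biological one named is cortisol. The outlier is one sentence, correct for cortisol and wrong for methylation. That makes the repair small; it does not remove the contradiction.

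2. **The aim is weak support.** The aim names genetic indices, but its list of how the indices will be assessed (cortisol, actigraphy, diaries, questionnaires) omits methylation. This stands in part. Methylation is nevertheless the only gene-based measure in the article, so the adjective has nothing else to refer to.

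3. **No analysis in the article would produce a false methylation effect.** A reader might infer that the plan specifies a B2-versus-B1 methylation test and will therefore generate spurious findings at some calculable rate. The article does not support that. Its mixed model for efficacy over time takes endpoints collected across the assessments, and a measure taken once has no time course to enter. The number of methylation tests and the correlation between genes are not stated either, so no family-wise error rate can be derived from the plan. The risk of misreading comes from the declared outcome role, not from a described model.

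4. **Later saliva could be assayed.** The follow-up swabs may make this physically possible, but it would contradict the two places that fix a single baseline assessment. Those would then be the passages in error, and a correction would still be needed.

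Two further inferences would go too far. The single sample is not useless: it can serve the biomarker purpose. And cortisol, although named in the same sentence, does not share the defect.

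**Conclusion.** The contradiction is real and can be checked from the article alone. Methylation is declared an outcome of an intervention that begins after its only measurement, so the trial can provide no information on a treatment effect on methylation.

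The reach is limited. Methylation is an additional outcome; the primary and secondary outcomes, the sample size and the main comparison are untouched. The point should be corrected because it changes what the trial may conclude, at almost no cost.

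The conclusion assumes that the single sample is taken at baseline as scheduled, and that the return of samples does not depend on the arm, so that a baseline difference is chance. The 0.05 rejection rate also assumes a two-sided test at the stated level.

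**What to change.** **Main change (wording only).**

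- In Salivary samples, limit the intervention-outcome sentence to cortisol, for example: *Cortisol will be evaluated as an outcome of the intervention. Methylation, measured once at baseline, will be studied only as a biomarker of poor sleep in pregnancy; no treatment effect on it will be inferred.*
- In Study aims, remove the reference to genetic indices from the effectiveness aim.
- Leave Additional outcomes as it stands. Suitable uses of the baseline sample include comparing Group A with Group B, or relating methylation to baseline ISI; the choice can be left to the analysis plan.

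The cost is a few words and the loss of a claim that the data could not have supported.

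**Only if a treatment effect on methylation is wanted.** Add a post-treatment methylation measurement to the baseline one, and change Additional outcomes and the one-assessment limit in Salivary samples to match. It should not replace the baseline sample: moving the only sample to after treatment would mix prenatal poor sleep with exposure to the intervention and defeat the biomarker purpose. This option costs a second round of sampling and sequencing, and a protocol amendment.
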